## Abstract

**Introduction::**

Malignant hyperthermia (MH) and exertional rhabdomyolysis (ERM) have long been considered episodic phenotypes occurring in response to external triggers in otherwise healthy individuals with variants in *RYR1*. However, recent studies have demonstrated a clinical and histopathological continuum between patients with *RYR1*-related congenital myopathies and those with ERM or MH susceptibility. Furthermore, animal studies have shown non-neuromuscular features such as a mild bleeding disorder and an immunological gain-of-function associated with MH/ERM related *RYR1* variants raising important questions for further research. Awareness of the neuromuscular disease spectrum and potential multisystem involvement in *RYR1*-related MH and ERM is essential to optimize the diagnostic work-up, improve counselling and and future treatment strategies for patients affected by these conditions. This study will examine in detail the nature and severity of continuous disease manifestations and their effect on daily life in patients with *RYR1*-related MH and ERM.

**Methods::**

The study protocol consists of four parts; an online questionnaire study, a clinical observational study, muscle imaging, and specific immunological studies. Patients with *RYR1*-related MH susceptibility and ERM will be included. The imaging, immunological and clinical studies will have a cross-sectional design, while the questionnaire study will be performed three times during a year to assess disease impact, daily living activities, fatigue and pain. The imaging study consists of muscle ultrasound and whole-body magnetic resonance imaging studies. For the immunological studies, peripheral mononuclear blood cells will be isolated for in vitro stimulation with toll-like receptor ligands, to examine the role of the immune system in the pathophysiology of *RYR1*-related MH and ERM.

**Discussion::**

This study will increase knowledge of the full spectrum of neuromuscular and multisystem features of *RYR1*-related MH and ERM and will establish a well-characterized baseline cohort for future studies on *RYR1*-related disorders. The results of this study are expected to improve recognition of *RYR1*-related symptoms, counselling and a more personalized approach to patients affected by these conditions. Furthermore, results will create new insights in the role of the immune system in the pathophysiology of MH and ERM.

**Trial registration::**

This study was pre-registered at ClinicalTrials.gov (ID: NCT04610619).

## Introduction

1

Variants in *RYR1,* the gene encoding for the ryanodine receptor-1 (RyR1), may lead to disturbances of calcium homeostasis in skeletal muscle and give rise to a wide variety of congenital myopathies including central core disease, multi-minicore disease, centronuclear myopathy and congenital fibre type disproportion.^[1,2]^ Moreover, *RYR1* variants account for a substantial proportion of patients presenting with episodic conditions as exertional rhabdomyolysis (ERM) and malignant hyperthermia (MH), a disorder that clinically manifests as a hypermetabolic crisis after exposure to volatile anesthetics and/or succinylcholine.^[3,4]^ These episodic phenotypes and *RYR1*-related myopathies have long been considered separate entities, however, recent studies have demonstrated a substantial clinical and histopathological overlap in patients with congenital myopathies and ERM or MH susceptibility.^[2,5–7]^

Although many studies on *RYR1-*related phenotypes have focused on the neuromuscular features, recent studies suggest multisystem involvement in *RYR1*-related diseases. A study in a knock-in mouse model with the MH-related *RYR1* variant Y522S showed that this variant leads to prolonged bleeding by altering vascular smooth muscle cell function.^[8]^ Another study in the same mouse model showed that this gain-of-function *RYR1* variant may offer selective immune advantages due to a more efficient specific immune response.^[9]^ A role of *RYR1* in the immune system is also supported by the identification of functional RyR1 s in human B-cells and dendritic cells.^[10–12]^ Furthermore, Epstein-Barr virus-immortalized B-cells from malignant hyperthermia susceptible (MHS) individuals carrying the V2168 M *RYR1* variant are more sensitive to the RyR1 to the RyR1 activator 4-Chloro-m-Cresol (4-CmC), and produced more interleukin (IL)-1β and IL-6 after treatment with 4-CmC and caffeine.^[13]^ This finding provides a potential explanation for the observation that ERM events often occur during or shortly after infections.^[14]^ Overall, these findings suggest multisystem disease manifestations associated with RyR1 dysfunction and raise important questions for further research. Therefore, a detailed study is needed to improve the knowledge of the neuromuscular and multisystem involvement of *RYR1*-related diseases, in patients with MH and ERM. This will enable health care professionals to recognize the whole spectrum of *RYR1*-related disease, thus improving the diagnostic work-up and counselling of patients with *RYR1* variants. Furthermore, better understanding of potentially associated immunological alterations in patients with *RYR1* variants will provide more insights in the immune system as a modifying factor in the pathophysiology of ERM and MH.

## Methods

2

### Study design

2.1

This study is a prospective, cross-sectional cohort study, and will be performed from August 2020 to August 2023 at the Radboud University Medical Centre and the Canisius Wilhelmina Hospital, Nijmegen, The Netherlands. The study protocol was approved by the regional medical ethics committee (CMO Arnhem–Nijmegen, registration number 2020-6251) and is pre-registered at ClinicalTrials.gov (ID: NCT04610619).

### Objective

2.2

The primary objective of this study is:

1.To investigate the full spectrum of disease manifestations of *RYR1*-related MH/ERM to optimize recognition, acknowledgement and counselling of *RYR1*-related complaints.

The secondary objectives are:

1.To establish a well-characterized baseline cohort for future studies on *RYR1*-related disorders;2.To investigate the role of the immune system as a potentially modifying factor in ERM and MH.

### Participants

2.3

Subjects will be recruited by the treating physicians from the MH and ERM cohorts at the national MH Investigation Unit in the Canisius Wilhelmina Hospital, Nijmegen and the neuromuscular outpatient clinic of the Radboud University Medical Centre, Nijmegen.

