#### Inclusion criteria

2.3.1

1.A history of MH susceptibility or ERM. MH susceptibility is defined as a pathogenic *RYR1* variant (www.emhg.org/diagnostic-mutations) or a positive in vitro contracture test (IVCT) according to the European Malignant Hyperthermia Group diagnostic guideline.^[15]^ A history of ERM is defined as at least one episode of clinical symptoms of rhabdomyolysis (cramps, myalgia, myoglobinuria, muscle weakness and/or muscle swelling) with a sudden increase (> 10.000 U/L) and a subsequent fall of creatine kinase (CK).^[16]^2.Genetically confirmed *RYR1* variant classified as pathogenic, likely pathogenic or a variant of unknown significance according to the variant curation expert panel recommendations for *RYR1* pathogenicity classifications in MH susceptibility.^[17]^3.Speak, read, write and understand Dutch fluently;4.Age ≥ 18 years old.

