#### Exclusion criteria

2.3.2

Patients with the following characteristics were excluded from participation in this study:

1.Patients with an initial presentation of a *RYR1*-related congenital myopathy, manifesting with muscle weakness;2.Other (neuromuscular) diseases resulting in muscle weakness;3.Patients with a contra-indication for magnetic resonance imaging (MRI);4.Symptoms of angina pectoris;5.Current malignancy;6.Patient using systemic steroids for a period > 14 days during the last 3 months;7.Pregnancy or breast-feeding.

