#### Additional exclusion criteria for the immunological studies

2.3.3

1.Diabetes mellitus;2.Established diagnosis of immune deficiency;3.Fever, surgery or trauma in the last 3 months;4.The use of statins in the last 12 months;5.Patient using systemic steroids for a period over 14 days during the last 12 months.

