### Study procedures

2.4

This study consists of four main parts, a questionnaire, clinical, imaging, and immunological part. A total of 20 patients will participate in all study parts while an additional 20 subjects will only participate in the questionnaire, clinical and imaging studies. Furthermore, the questionnaire study is open to all patients meeting the inclusion criteria, without participation in the other study parts. The study design is summarized in Figure 1.

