### Statistical analysis

2.5

Continuous variables will be summarized by their mean and standard deviation or median and interquartile ranges depending on its distribution. Categorical data, including ordinal data, will be summarized in terms of percentages. Results from the questionnaire studies and cytokine production from *RYR1* patients will be compared to normal values and (if applicable) healthy controls using the students *t*-test.

Due to the explorative nature of this study we did not perform a power calculation. For the clinical and imaging studies, 40 subjects will be included since previous studies and case series with similar sample size showed a substantial clinical and histopathological overlap in patients with congenital myopathies and ERM or MH susceptibility.^[3,5,6]^ For the immunological studies, 20 MHS/ERM patients and 40 healthy controls will be included as previous studies in animal models showed an immunological gain-of-function in MHS mice in a lower number of subjects.^[12,13]^ The number of healthy controls is twice the number of MHS/ERM subjects as more variance is expected in the healthy controls than in the MHS/ERM subjects.

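### Relatives can enter the patient group, but Student's t-test treats patients as independent, so questionnaire p-values against norms are too small if relatives enrol and their outcomes correlate

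*Protocol article*

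**What the plan says.** All references are to the protocol article.

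- **2.3 Participants.** "Subjects will be recruited by the treating physicians from the MH and ERM cohorts at the national MH Investigation Unit" and from the Radboud neuromuscular outpatient clinic. Entry is not restricted to index patients.
- **2.3.1 Inclusion criteria.** "MH susceptibility is defined as a pathogenic" RYR1 variant on the cited diagnostic list, or a positive in vitro contracture test (IVCT). The alternative route is a personal episode of exertional rhabdomyolysis (ERM). A second criterion requires a "Genetically confirmed *RYR1* variant classified as pathogenic, likely pathogenic or a variant of unknown significance".
- **2.3.2 and 2.3.3 Exclusion criteria.** There are seven general and five immunology-specific criteria. None concerns relatedness to another participant.
- **2.4 Study procedures.** Forty patients enter the questionnaire, clinical and imaging parts, and 20 of them also enter the immunological part. In addition, "the questionnaire study is open to all patients meeting the inclusion criteria, without participation in the other study parts".
- **2.4.4 Immunology.** The 40 controls are hospital staff volunteers.
- **2.5 Statistical analysis.** Questionnaire results and cytokine production from RYR1 "patients will be compared to normal values and (if applicable) healthy controls" with Student's t-test. More variance is expected in controls than in patients. No test is named for clinical or imaging data, and no significance level is given.

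**The concern.** RYR1 variants run in families. Under 2.3.1, an adult found to carry the family's listed variant qualifies with no event of their own. A cohort of carriers can therefore hold several members of one family, and nothing in the criteria stops them all from enrolling. The questionnaire part, which has open enrolment, is the most exposed.

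Relatives share the variant under study as well as genetic and home background, so positive correlation in fatigue, pain, worry or cytokine response is plausible. Student's t-test computes its standard error as if every patient contributed independent information. With positive within-family correlation that standard error is too small, and differences from normal values reach significance too often. Staff controls would not be expected to be clustered in this way, so in the cytokine contrast the problem sits in the patient group only.

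The descriptive results are touched too: one family of four would be 4/40 = 10% of the clinical and imaging sample.

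**Working it through.** The plan gives no power calculation or error rate to reproduce.

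**Inputs from the article:** 40 patients in the clinical and imaging parts, who also fill in the questionnaires; 20 patients and 40 controls for cytokines; Student's t-test; larger variance expected in controls, size not given.

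**Assumptions:** two-sided 5% level; equal family sizes m; ICC 0.1 to 0.5; ratio k of control SD to patient SD of 1, 1.25 or 1.5.

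**Step 1. Design effect.** DE = 1 + (m − 1) × ICC.

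| Families | ICC | DE | 40 patients are worth |
|---|---|---|---|
| pairs | 0.1 | 1.1 | 40/1.1 = 36.4 |
| pairs | 0.3 | 1.3 | 40/1.3 = 30.8 |
| pairs | 0.5 | 1.5 | 40/1.5 = 26.7 |
| fours | 0.3 | 1.9 | 40/1.9 = 21.1 |

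**Step 2. Comparison with a fixed norm.** The t-test ignores DE, so its actual error is about 2 × [1 − Φ(1.96/√DE)]. This gives 6.2%, 8.6%, 11.0% and 15.5% for the four rows. Simulation of the one-sample t-test with n = 40 (100,000 runs) gives 6.1%, 8.5%, 11.0% and 15.5%. With n = 20 the results are almost the same (6.0%, 8.7%, 11.1%, 15.9%). The inflation follows family size and ICC, hardly the number of patients, so the open-ended questionnaire sample does not change the picture.

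**Step 3. Cytokine contrast, 20 against 40.** With patient variance set to 1:

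- true variance of the difference: DE/20 + k²/40
- variance the pooled test uses: 0.075 × (19 + 39k²)/58

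For pairs at ICC 0.3:

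- k = 1: 0.090 against 0.075, ratio 1.20, so the test is too liberal.
- k = 1.25: 0.1041 against 0.1034, ratio 1.01, so the two effects cancel.
- k = 1.5: 0.1213 against 0.1380, ratio 0.88, so the test is conservative.

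Simulated error of the pooled test:

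| Families, ICC | k = 1 | k = 1.25 | k = 1.5 |
|---|---|---|---|
| none | 5.0% | 3.5% | 2.7% |
| pairs, 0.1 | 5.8% | 4.0% | 3.0% |
| pairs, 0.3 | 7.5% | 5.1% | 3.7% |
| pairs, 0.5 | 9.0% | 6.3% | 4.5% |
| fours, 0.3 | 12.2% | 8.7% | 6.2% |

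The offset belongs to the pooled test. With Welch's test on individual patients at k = 1.5, pairs at ICC 0.3 give 6.7% and fours 10.2%.

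**Step 4. Does a remedy hold its level?** For 20 against 40 at equal variances, ordinary cluster-robust errors (usual finite-sample factor, t on the number of clusters minus 1) give 6.3–6.5% for pairs and 9.7% for fours at ICC 0.3, so they do not restore 5% with this few families. Welch's t-test on family means gives 4.9–5.7%.

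**The case against.** The strongest reply is that this is a condensed article. Family identifiers and clustered errors are details that a full protocol or analysis plan may hold, and no passage mentions relatives at all. Part of this stands: the documents do not show that relatives will enrol, and every size above is assumed. But the article does state the eligibility route, the recruitment source and the test, and the named test does not suit the population that the named criteria admit. The random selection claimed in the Discussion does not help, because a random draw of individuals from a cohort containing relatives can draw relatives.

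Other readings that a reader might infer go too far:

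- **Any carrier qualifies.** Only a variant on the cited list suffices by itself. Carriers of likely pathogenic variants or variants of unknown significance also need a positive IVCT or an ERM episode.
- **The cytokine test exceeds 5%.** This is not established. Section 2.5 expects larger control variance, and with the larger group also the more variable one, the pooled test is conservative. For pairs this can cancel the inflation.
- **Clinical and imaging tests are invalid.** Section 2.5 names no test for those data. Means, medians and percentages as summaries do not rely on independence, and no intervals are announced.

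The study is also exploratory, with no power calculation and no decision that hangs on a p-value. That lowers the stakes, but does not make the p-values against norms correct.

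**Conclusion.** The point holds in conditional form. The entry criteria allow relatives, and the named test ignores family. If relatives enrol and their outcomes correlate positively, the questionnaire comparisons with normal values reject too often: about 6–11% for pairs over ICC 0.1–0.5, and about 16% for families of four at ICC 0.3, instead of 5%. For cytokines the same pairs give 5.8–9.0% under equal variances. The expected larger control variance can remove that for pairs, while families of four at ICC 0.3 still give 6.2–8.7% at the assumed SD ratios of 1.5 and 1.25.

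This rests on assumed family sizes, ICCs, SD ratios and a 5% level, none of which the article gives. If each patient comes from a different family, the comparisons with norms keep their 5% level. No stated sample size is shown to be wrong.

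**What to change.** 1. Record a family identifier and the specific RYR1 variant for every patient, including those in the questionnaire part only. Report the number of families in each part.
2. In 2.5, replace the plain t-test for the questionnaire and cytokine comparisons with a family-aware method suited to few clusters: for example, t-tests on family means (Welch's version for cytokines), or a mixed model or cluster-robust errors with a small-sample correction. Ordinary cluster-robust errors are not enough here. Family means weight each family equally, so state that choice.
3. Add a sensitivity analysis with one patient per family, chosen by a rule fixed beforehand.
4. For the descriptive clinical and imaging results, report the number of families, and use family-aware intervals only if intervals are given.

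The cost is one data field and a few sentences, with no change to eligibility or sample size. If relatives enrol, intervals widen by the square root of the design effect: √1.1 = 1.05 to √1.9 = 1.38, or roughly 5–40% over the assumed range. The smaller number of degrees of freedom adds somewhat to that when families are few. If none enrol, the identifier changes nothing. It should be collected at enrolment, since relatedness may be hard to reconstruct later and the cohort is meant as a baseline for future studies.

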#### Inclusion criteria

2.3.1

1.A history of MH susceptibility or ERM. MH susceptibility is defined as a pathogenic *RYR1* variant (www.emhg.org/diagnostic-mutations) or a positive in vitro contracture test (IVCT) according to the European Malignant Hyperthermia Group diagnostic guideline.^[15]^ A history of ERM is defined as at least one episode of clinical symptoms of rhabdomyolysis (cramps, myalgia, myoglobinuria, muscle weakness and/or muscle swelling) with a sudden increase (> 10.000 U/L) and a subsequent fall of creatine kinase (CK).^[16]^2.Genetically confirmed *RYR1* variant classified as pathogenic, likely pathogenic or a variant of unknown significance according to the variant curation expert panel recommendations for *RYR1* pathogenicity classifications in MH susceptibility.^[17]^3.Speak, read, write and understand Dutch fluently;4.Age ≥ 18 years old.

#### Exclusion criteria

2.3.2

Patients with the following characteristics were excluded from participation in this study:

1.Patients with an initial presentation of a *RYR1*-related congenital myopathy, manifesting with muscle weakness;2.Other (neuromuscular) diseases resulting in muscle weakness;3.Patients with a contra-indication for magnetic resonance imaging (MRI);4.Symptoms of angina pectoris;5.Current malignancy;6.Patient using systemic steroids for a period > 14 days during the last 3 months;7.Pregnancy or breast-feeding.

#### Additional exclusion criteria for the immunological studies

2.3.3

1.Diabetes mellitus;2.Established diagnosis of immune deficiency;3.Fever, surgery or trauma in the last 3 months;4.The use of statins in the last 12 months;5.Patient using systemic steroids for a period over 14 days during the last 12 months.

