#### Part 4: Immunology

2.4.4

Immunological investigations will include a set of laboratory studies using blood samples from a subset of 20 *RYR1* patients and 40 age and sex matched healthy controls. Healthy controls will be recruited amongst volunteers from the staff members of the Radboud University Medical Centre and the Canisius Wilhelmina Hospital.

Peripheral mononuclear blood cells (PBMC) will be isolated from EDTA blood of *RYR1* patients and healthy controls. PBMCs will be stimulated for 24 hours with the Toll-like receptor (TLR) ligands *Escherichia coli* lipopolysaccharide (LPS) and heat-killed Candida in the presence of RyR1 agonists 4-CmC and caffeine and/or the RyR1 antagonist dantrolene. Cytokine levels (IL-1β, IL-6 and TNF-α) in the supernatant of the ERM/MHS subjects will be compared to healthy controls.^[9,12,13]^ Additionally, circulating cytokines (IL-1β, IL-6) will be measured in all participating patients.^[9]^

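### The steroid exclusion for the immunological studies is set by duration only, so a patient on a course of 14 days or less at the blood draw is eligible for the cytokine comparison

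*Protocol article*

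**What the plan says.** Two steroid criteria apply to patients in the immunology part:

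- Study-wide (protocol article, 2.3.2): "Patient using systemic steroids for a period > 14 days during the last 3 months".
- Immunology only (2.3.3): "Patient using systemic steroids for a period over 14 days during the last 12 months".

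Section 2.3.3 also lists "Fever, surgery or trauma in the last 3 months" and "The use of statins in the last 12 months", besides diabetes and immune deficiency. The statin item has no minimum duration.

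Section 2.4.4 plans 24-hour stimulation of blood cells from 20 patients and 40 healthy controls and compares IL-1β, IL-6 and TNF-α in the supernatant. Section 2.5 names Student's t-test and says that no power calculation was done. Section 2.4.4 introduces the blood work as concerning 20 of the patients, but ends by saying that "circulating cytokines (IL-1β, IL-6) will be measured in all participating patients". Section 2.4 divides the clinic patients as follows: "A total of 20 patients will participate in all study parts while an additional 20 subjects will only participate in the questionnaire, clinical and imaging".

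**The concern.** For an assay on freshly drawn cells, a drug in the body at sampling matters more than one stopped months earlier. The steroid rule looks only at how long a course lasted within a look-back window. Someone on day 10 of a course at the draw passes both criteria, while someone who finished a 15-day course eleven months earlier does not. The plan itself treats drug exposure as a threat to this assay: it lengthens the steroid window from 3 to 12 months for the immunology part and excludes any statin use over the same period. A current short steroid course is the gap that remains.

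The direction matters. The Introduction and section 2.5 point to an immune gain of function, with more IL-1β and IL-6. Steroid suppression works against that signal, in a small comparison that serves a secondary objective (2.2).

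A second, smaller matter is that the text does not say clearly whose circulating cytokines are measured, and hence whether 2.3.3 covers all of them.

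**Working it through.** **Eligibility, read side by side**

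| Steroid exposure | 2.3.2 (more than 14 days in 3 months) | 2.3.3 (more than 14 days in 12 months) | Eligible for immunology? |
|---|---|---|---|
| 15-day course ended 11 months ago | passes | fails | no |
| Ongoing use, already beyond 14 days | fails | fails | no |
| Day 10 of a course on the day of the draw | passes | passes | yes |

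The two windows differ because they serve different parts of the study. That is not a contradiction. The gap is the third row.

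**Scale**

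The article gives no effect size, SD, alpha or power, so there is no stated figure to reproduce. Assumptions: SD 1, two-sided alpha 0.05, 80% power.

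Detectable difference, 20 against 40, by the normal approximation: (1.960 + 0.842) × √(1/20 + 1/40) = 2.802 × 0.2739 = 0.77 SD. The t-distribution gives 0.78 SD.

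Suppose k of the 20 patients are on a short course that lowers a cytokine by s SD. Neither k nor s is in the documents. The group mean shifts by k × s / 20. Student's t-test was simulated (40,000 runs per setting), once with no RYR1 effect and once with a true increase of 0.78 SD.

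| k of 20 | Mean lowered by (s = 1 to 2) | False-positive rate, no RYR1 effect | Power, true increase 0.78 SD |
|---|---|---|---|
| 0 | 0 | 5% | 80% |
| 1 | 0.05 to 0.10 SD | about 5 to 6% | about 74 to 66% |
| 2 | 0.10 to 0.20 SD | about 6 to 9% | about 68 to 51% |
| 4 | 0.20 to 0.40 SD | about 10 to 23% | about 53 to 22% |

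The extra false positives point towards lower cytokines in patients. The power loss is the masking of a gain of function.

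**Circulating cytokines**

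- Narrow reading, only the Part 4 patients: 0 of 20 fall outside screening against 2.3.3.
- Wide reading, all 40 clinic patients: 20/40 = 50% would not have been screened against 2.3.3.

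Section 2.4 confines the second 20 to non-immunology parts. It therefore favours the narrow reading, or contradicts the wide one.

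**The case against.** **The gap is narrow.** The rule removes every current user who has passed 14 days, and the 3-month exclusion for fever, surgery or trauma removes some of the reasons for a short course. Section 2.4.2 collects current medication from the health records, so an exposed patient might be recognised afterwards. All of this stands and limits how many patients are likely to be affected. None of it makes such a patient ineligible, and no rule is stated for handling one who is recognised.

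**The study is exploratory and the objective secondary.** This is true and keeps the point in proportion. It does not make a badly placed threshold harmless in a comparison with 20 patients.

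**Other immunosuppressants.** A reader might fault the article for listing no immunomodulating drug other than steroids and statins. A condensed article commonly leaves a full drug list to the protocol, so that omission is not held against the plan. The steroid rule differs because it is stated, and its stated form admits current short courses.

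**Circulating cytokines in unscreened patients.** A reader might infer from "will be measured in all participating patients" that IL-1β and IL-6 are planned in patients who need not meet the immunology criteria. The article does not establish this. The sentence sits in the immunology part, 2.3.3 is headed as applying to the immunological studies, and 2.4 says that "A total of 20 patients will participate in all study parts" and limits the other 20. Taken fully literally, the phrase would also include questionnaire-only participants. What remains is an ambiguity.

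**Recent infection as a driver of the results.** A reader might also infer this, but the 3-month fever criterion largely closes that route for Part 4 patients. It stays open only for infection without fever, or under the wide reading.

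**Conclusion.** The point holds for the steroid criterion. As written, 2.3.2 and 2.3.3 together admit a patient who is taking systemic steroids at the blood draw, provided that the course is 14 days or less. The likely bias runs against the gain of function being sought.

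The size is unknown because the number of such patients is not given. With one or two exposed patients, and an assumed suppression of 1 to 2 SD, the mean shift is at most 0.20 SD and the false-positive rate stays at or below about 9%: a modest distortion. The loss of power is more noticeable at the pessimistic end (two patients, 2 SD: about 51% instead of 80%). With no exposed patients there is no effect. That steroids suppress these cytokines is assumed here; the article gives no figure for it, although its own stricter immunology criterion implies the concern.

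For circulating cytokines, the finding is only that 2.4.4 and 2.4 must be reconciled.

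**What to change.** 1. Add to 2.3.3 an exclusion from, or deferral of, the research blood draw for any systemic steroid or other systemic immunomodulating drug in current use or used within a pre-specified short window before sampling. Apply it to patients and healthy controls alike. Keep the 12-month rule for longer courses. This governs research eligibility and the timing of sampling only; it does not touch anyone's treatment.
2. Ask about these drugs on the day of the draw and record the answer, rather than relying on health records alone.
3. In 2.4.4, state which patients have circulating cytokines measured and that 2.3.3 applies to them, and bring 2.4 into line. If all 40 clinic patients are meant, collect the 2.3.3 items for the second 20 and analyse those who fail them separately.

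The cost is a change of wording, a few screening questions, and an occasional deferred draw or replaced immunology participant.
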